### Sample Size

We will enroll 300 participants and anticipate that at least 250 (n=125, 50% per arm) will have the 6-month postintervention follow-up data. For the primary end point of the Perceived Stress Scale (PSS), this sample size has >80% power to detect a 3-point difference in mean PSS scores at follow-up using an *F* test in an analysis of covariance. This assumes the R-squared value of 5 covariates, including baseline PSS, to be 0.3 and uses a significance level of α=.05. This calculation conservatively estimates the SD of PSS to be 10 points. Initial psychometric studies and norm groups analysis of the PSS reported SDs of 7.2 points in African Americans; relevant to the RiSE study, group SDs ranged from 6 to 10 points from a pilot trial involving African Americans with hypertension [127]. At this sample size and with similar design assumptions, effect sizes were estimated using the RiSE pilot study for the hypothesized mediator of coping as well as biomarkers [48]. The estimates from the analysis of covariance (Table 4) represent the lower limits for power because the mixed model approach that incorporates all time points may be more powerful in detecting meaningful differences.

**Table 4 table4:** Pilot study estimates and effect sizes.

Outcome evaluated at 6 months	RiSE^a^ group, mean	Control group, mean	|Δ|, mean	Pooled SD	Observed effect size	Mean difference required for 80% power^b^
WCQ^c^: active coping	23.76	24.77	1.01	8.24	0.06	2.45
WCQ: avoidance coping	8.14	14.38	6.24	5.25	0.59	1.56
WCQ: minimize situation	11.21	14.04	2.83	4.36	0.32	1.30
TNF-α^d^	0.95	1.00	0.05	0.36	0.07	0.11
hsCRP^e^	3.83	7.24	3.41	6.30	0.27	1.88

^a^RiSE: Resilience, Stress, and Ethnicity.

^b^Assumes n=125 per group and α=.05; R-squared value of 5 covariates is 0.30.

^c^WCQ: Ways of Coping Questionnaire.

^d^TNF-α: tumor necrosis factor–alpha.

^e^hsCRP: high-sensitivity C-reactive protein.

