**Exclusion criteria**
History of myocardial infarction or ischemic heart disease and angina pectoris, stent placement, coronary artery bypass, left ventricular hypertrophy, congestive heart failure, or ischemic strokeAny major immune-related disease (eg, rheumatoid arthritis or lupus)Use of immune-altering medications, such as glucocorticoidsPeriodontal disease, bleeding gums, and dental work in the past 72 hCurrent smoker or has smoked in the past 3 moActive cancerActive infectionSubstance abuseCognitive or psychiatric disorder that would affect the ability to participate in program classes (Brief Screen for Cognitive Impairment total score of ≥8)

Participants will be assessed for CMD risk. They will also be assessed for cognitive impairment using the 3-item Brief Screen for Cognitive Impairment [71]: a total score of ≥8, which suggests cognitive impairment, will lead to the exclusion of the participant from the study. All ineligible participants will receive a gift card (US $10) after the screening. Baseline measures will be collected after the screening.

After the baseline interview (T0), eligible participants will be randomized 1:1 to RiSE or HEP, with each wave of enrollment treated as a block. The randomization plan (PROC PLAN) generated in SAS 9.4 (SAS Institute Inc) includes the site as a stratifying variable, and we plan for each site to have at least 6 RiSE and 6 control participants per wave. Patient registration data, group assignment, and self-report survey data will be managed via a single REDCap (Research Electronic Data Capture; Vanderbilt University) server with access for both sites.

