### Intervention

#### Overview

Both RiSE and HEP groups will meet weekly on Zoom (Zoom Communications, Inc) for 8 consecutive weeks for approximately 2 hours per session. In addition, 2 sessions will occur 1 month and 2 months after the completion of the interventions. These booster sessions will include a brief review of information covered during the programs and will allow the participants the opportunity to discuss and ask questions about how they applied what they learned in their lives. For every class attended, participants will receive a US $30 gift card. Participants will be sent an SMS text message or email reminder before each class. The RiSE and HEP classes will meet synchronously over Zoom and will be led by experts in the area. The study staff will review how to access Zoom with research participants at the baseline data collection appointment and will answer any questions they may have. The topics of each session are detailed in Table 2. Written educational materials will be provided to support the classes in both interventions.

**Table 2 table2:** Overview of the Resilience, Stress, and Ethnicity (RiSE) intervention and health education program (HEP) topics.

Session	RiSE program (intervention)	HEP (active control)
1	Introduction to RiSE; establish group as safe place for dialogue about racism and oppression	Introduction to HEP
2	Explore issues related to being a woman from a minoritized community and impact of intersectionality; discuss insidious forms of racism	Caring for your skin cleansers and makeup
3	Explore challenges in having conversations about race and racism and discuss how defensiveness makes conversations unproductive	Cooking organically
4	Identify both overt and covert racism; reflect how racism can affect emotions and esteem	Finding credible health care information on the web
5	Identify aversive racism, institutional racism, and the role of White privilege; reflect on how these forms of racism can affect emotions and esteem	Immunizations for adults—what is available and what do you need?
6	Describe the use of cognitive behavioral theory to conceptualize emotional reactions to race-based stress	Over-the-counter medications: potential hazards
7	Review physical reactions to stress; practice strategies to cope with stress	Growing an herb garden
8	Review resilience, coping, and empowerment in response to race-based stress	Communicating with the health care team

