#### Statistical Analysis

Baseline demographics and clinical characteristics will be reported according to the CONSORT (Consolidated Standards of Reporting Trials) guidelines. The size of any chance group imbalances will be described, but no formal significance testing of group differences will be performed [124]. Generalized linear mixed models (GLMMs) will be used for analyses of outcomes due to their flexibility regarding the distribution of dependent variables (DVs) and their superiority over alternative approaches such as repeated measures ANOVA for longitudinal modeling with missing data. Data will be collected from participants at 4 time points (T0: baseline, T1: midintervention; 4 wk, T2: intervention completion; 8 wk, and T3: 6 mo after intervention completion). Time will be modeled as a fixed effect, and random intercepts and random slopes will be considered to account for within-individual differences and trends. The primary DVs include stress-related symptoms (current perceived stress, depressive symptoms, fatigue, and sleep disturbance) and biomarkers (ie, IL-6, TNF-α, IL-1β, IFN-γ, and CRP) to be modeled using GLMM. Before modeling, DVs will be plotted to choose an optimal distribution and link function for GLMMs and to identify potential floor or ceiling effects. For each DV, a GLMM will regress the follow-up DV on a group×time interaction, the baseline value of the DV, and covariates. Treatment assignment (group) will be a fixed effect, and adjusted means with SEs will be used to describe group differences. Random effects will be evaluated for site and cohort. Exploratory end points include coping (Ways of Coping Questionnaire and Coping with Discrimination Scale), internalizing racism (Appropriated Racial Oppression Scale), and resistance to racism (Resistance and Empowerment Against Racism), which will be DVs in separate GLMMs, as described earlier.

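### The power calculation leaves out class clustering, and the named site and cohort random effects are not at class level

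*Protocol article*

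**What the plan says.** The Sample Size section plans as follows: "We will enroll 300 participants and anticipate that at least 250 (n=125, 50% per arm) will have the 6-month postintervention follow-up data". It then states that "this sample size has >80% power to detect a 3-point difference in mean PSS scores at follow-up", using an ANCOVA F test. On the other inputs it says: "This assumes the R-squared value of 5 covariates, including baseline PSS, to be 0.3 and uses a significance level of α=.05". The SD is set at 10 points and called conservative; SDs of 7.2, and of 6 to 10, are cited from other data. No class size, ICC or design effect appears. The section adds: "The estimates from the analysis of covariance (Table 4) represent the lower limits for power", on the ground that a mixed model using all time points may be more powerful.

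On delivery, the Intervention Overview says: "Both RiSE and HEP groups will meet weekly on Zoom". There are eight weekly sessions of about two hours and two boosters. The RiSE Intervention section treats the group format as one of the mechanisms of effect, and the fidelity text under HEP Intervention plans to measure group cohesion and control for it.

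On allocation, Procedures randomizes women 1:1 with each enrollment wave as a block, stratified by site, and adds: "we plan for each site to have at least 6 RiSE and 6 control participants per wave". Every wave therefore contains both arms.

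On the model, Statistical Analysis considers participant-level random intercepts and slopes and then says: "Random effects will be evaluated for site and cohort". No class or arm x cohort term is named.

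**The concern.** Women who share a class for eight weeks and two boosters may have correlated outcomes, and the article itself expects group process to matter. The relevant cluster is the class, which is one arm within one wave (or one arm within one wave and site). Two consequences follow if that correlation is positive.

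First, the RiSE-HEP difference is less precise than the sample-size calculation assumes, so power for the Perceived Stress Scale (PSS) is lower than stated for the same SD.

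Second, a cohort or site intercept is common to both arms and drops out of the arm comparison. A model with only those intercepts would report a standard error that omits class variance, and a true null would be rejected more than 5% of the time. This second point bears on the validity of the primary test.

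**Working it through.** **Inputs from the article.** 125 analysed women per arm; difference 3 points; SD 10; R-squared 0.30; α = 0.05 (Sample Size). Cohorts of 22 to 26 women, mean 120/5 = 24 (Table 5). Expected follow-up 250/300 = 83%.

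**Assumptions.** The ICC is not given; 0.01 to 0.05 is used. The number of classes per arm per wave is not given either. With one class per arm per wave, analysed class size is m = (24/2) × 250/300 = 10, giving 250/10 = 25 classes and 25 − 2 = 23 between-class df. If each site runs its own class, m is about 5, giving 50 classes and 48 df.

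**Step 1: reproduce the stated power.**
- Residual SD = 10 × √(1 − 0.30) = 8.37.
- SE = 8.37 × √(2/125) = 1.058.
- The noncentral F with 1 and 243 df gives 80.6%; the normal approximation gives 80.9%.
- The last column of Table 4 also reproduces with (1.96 + 0.84) × SD × √0.7 × √(2/125): 2.44, 1.56, 1.29, 0.107 and 1.87, against the printed 2.45, 1.56, 1.30, 0.11 and 1.88.

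Both results assume independent women; no design effect was applied.

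**Step 2: headroom.** (3/1.058)² = 8.04 and (1.96 + 0.84)² = 7.85, so the largest design effect that keeps 80% is 8.04/7.85 = 1.024. From 1 + (m − 1) × ICC = 1.024, the break-even ICC is about 0.003 for m = 10 and 0.006 for m = 5 (normal approximation, SD 10).

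**Step 3: power with class clustering, SD 10.** SE = 1.058 × √(1 + (m − 1) × ICC), with t tests on class-level df.

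| m (df) | ICC | Design effect | Power for 3 points | Difference for 80% power |
|---|---|---|---|---|
| 10 (23) | 0.01 | 1.09 | 74% | 3.2 |
| 10 (23) | 0.02 | 1.18 | 71% | 3.4 |
| 10 (23) | 0.05 | 1.45 | 62% | 3.7 |
| 5 (48) | 0.01 | 1.04 | 78% | 3.1 |
| 5 (48) | 0.02 | 1.08 | 76% | 3.1 |
| 5 (48) | 0.05 | 1.20 | 72% | 3.3 |

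Part of the loss comes from the df alone: at ICC 0, power is 77.5% on 23 df and 79.3% on 48 df. On ordinary df with m = 10, power is 77.5% at ICC 0.01 and 65.3% at 0.05.

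**Step 4: a smaller SD.** With SD 7.2 and m = 10, power at ICC 0.05 is 90.5% on the normal approximation and 87.9% on 23 df. It stays above 80% up to an ICC of about 0.11 (normal) or 0.09 (23 df).

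**Step 5: type I error.** Write each class mean as cohort effect + class effect + error. Subtracting HEP from RiSE within a cohort removes the cohort effect and leaves the difference of two class effects, which a cohort intercept does not model. Ignoring class variance altogether gives 2 × (1 − Φ(1.96/√design effect)): 7.1% at ICC 0.02 and 10.4% at 0.05 for m = 10, and 5.9% and 7.4% for m = 5. A simulation with a cohort intercept only (20,000 runs, 13 cohorts × 2 arms × 10 women) gave 7.2% at ICC 0.02 and 10.8% at 0.05. At 0.05 the model SE averaged 1.02 against a true 1.25, while a class-level analysis rejected 5.3%. These rates depend on ICC and class size, not on the SD.

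**The case against.** A reader might infer that the trial is underpowered for 3 points. The documents do not support that. The loss needs a positive class ICC at six months, and none is given. SD 10 is the top of the cited range; at 7.2 the margin absorbs a sizeable ICC (Step 4). Follow-up above 250 would also help: with 140 analysed per arm, power on the normal approximation is 81.5% at ICC 0.01, though 78.1% at 0.02. The same two RiSE interventionists using standardized materials throughout may keep the ICC small.

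A reader might also infer that the planned model treats all women as independent, or that its false-positive rate is already known to exceed 5%. That goes too far. Random effects for site and cohort are to be evaluated, and the text does not say they are intercepts only: a treatment effect varying randomly by cohort would carry arm x cohort variance. A detailed analysis plan is still to be finalized before database lock and may specify this.

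Finally, the lower-limits sentence points to Table 4, which holds coping and biomarker outcomes and no PSS row, and its reason is hedged.

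These points make the size conditional. They do not remove the fault. The power figure as printed excludes class clustering, the only random effects named above the participant are at a level shared by both arms, and a smaller SD does nothing for type I error. The cohesion score is a measured covariate and does not replace a class variance component. Extra time points may add precision within women but do not remove between-class variance, so the lower-limit claim is unsupported for the Table 4 outcomes too.

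**Conclusion.** The concern holds in conditional form. The stated power (80.6% on its own inputs) has room for a design effect of only about 1.02 and assumes classmates are independent, and no class-level term is named in the model.

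For an assumed ICC of 0.01 to 0.05 at SD 10, on class-level df, power falls to about 74% to 62% with one class per arm per wave, or about 78% to 72% with site classes. If the SD is nearer 7.2, power for 3 points is not in doubt over that ICC range.

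The type I error risk is the more important part because no SD margin offsets it. It arises if the analysis is run with cohort or site intercepts only and the class ICC is positive. ICC and class size are assumptions throughout.

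**What to change.** 1. Include a random effect for class (arm x cohort, or arm x cohort x site if classes are run by site) in every outcome model. Keep it whatever its estimated size, and use small-sample degrees of freedom such as Kenward-Roger. Site and cohort can stay as further effects.
2. State how many classes run per arm per wave. Restate PSS power over a stated range of ICC, class size and SD, with power and detectable difference on the same degrees of freedom. For SD 10 and ICC 0.01 to 0.05, the matching pairs are 74% to 62% with 3.2 to 3.7 points (m = 10, 23 df), or 78% to 72% with 3.1 to 3.3 points (m = 5, 48 df).
3. Qualify or delete the statement that the ANCOVA estimates are lower limits for power.

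The cost is one extra variance component and a less favourable power statement. No extra participants are needed, and the change can be made in the analysis plan before database lock.

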## Results

This study was funded by the National Institute on Aging on March 30, 2023, with a project end date of January 31, 2028. Recruitment and enrollment began in October 2023 and is ongoing. As of March 2025, we enrolled 120 participants. Figure 3 depicts the CONSORT flow diagram for study participants as of March 2025.

**Figure 3 figure3:**
[figure not shown]
CONSORT (Consolidated Standards of Reporting Trials) flow diagram for the study. RiSE: Resilience, Stress, and Ethnicity.

Table 5 presents the start dates and enrollment for each cohort. We plan to enroll 3 cohorts each year with anticipated enrollment completed in 2027. In addition, retention (defined as attending at least 5 of the 8 program classes) has been 95% (38/40) for the RiSE intervention and 91% (41/45) for the HEP active control intervention. We began preliminary analysis of baseline data in March 2025.

**Table 5 table5:** Cohort start dates and enrollment size (n=120).

Cohort	Start date	Participants, n (%)
1	October 30, 2023	23 (19.2)
2	February 26, 2024	23 (19.2)
3	May 7, 2024	26 (21.7)
4	September 16, 2024	26 (21.7)
5	February 17, 2025	22 (18.3)

## Discussion

### Principal Findings

This study proposes to examine the effect of a race-based stress reduction intervention, called RiSE, on stress-related symptoms, coping, and inflammation in older African American women at risk for CMD. We anticipate that participants completing the RiSE program will have decreased stress-related symptoms, improved adaptive coping, and decreased inflammatory burden compared to those randomized to the active control group (HEP).

Racism is dangerous, pervasive, and unfortunately a growing problem in the United States. A third of African Americans report experiencing a race-related incident in the past year [128]. Undeniably, racism needs to be addressed at the interpersonal, community, and societal levels. However, until such time, ways to reduce the impact of racism on psychological and physical health at the individual level must be developed and tested. The RiSE intervention may accomplish this goal. It reduces stress and has the potential to reduce the psychobiological consequences of racism and discrimination, leading to decreased inflammation and ultimately contributing to lowered CMD and CVD risk in African American women. In sum, despite evidence that experiencing racism and perceived discrimination heightens the inflammatory response and CMD [19,53], few evidence-based interventions are available to help individuals from minoritized communities cope with unique stressors related to their racial or ethnic identity. There is evidence that health behaviors [129], early life adversity [130,131], and ethnic identity [132-134] may impact the relationships among chronic stressors (perceived discrimination, racism, and subjective social status) and the psychological and inflammatory response to stress.

### Limitations and Strengths

The proposed study has some limitations that should be recognized. As with most RCTs, challenges related to recruitment and retention are anticipated. In response, we have developed a detailed recruitment plan supported by our community advisory board as well as strategies to minimize attrition, including immediately contacting participants who miss program classes or data collection visits as well as providing fair compensation. In addition, generalizability is a potential limitation of this study. Future work will examine RiSE in additional populations. Despite these challenges, this study will be one of the first to examine a race-based stress reduction intervention in African American women and has the potential to improve the health of minoritized groups faced with the chronic stress associated with experiencing racism and discrimination [35,39-45,48,55] ([name], unpublished data, November 2017). In addition, RiSE is being offered via Zoom, which may allow participants who cannot travel or have caregiving responsibilities the opportunity to participate in the program. If RiSE is found to be effective in older African American women, future research may consider evaluating RiSE in other populations, such as younger African American women as well as men.

## Abbreviations

CBT: cognitive behavioral therapy
CMD: cardiometabolic disease
CONSORT: Consolidated Standards of Reporting Trials
CRP: C-reactive protein
CVD: cardiovascular disease
DV: dependent variable
GLMM: generalized linear mixed model
HEP: health education program
IFN-γ: interferon-gamma
IL-1β: interleukin-1beta
IL-6: interleukin-6
MBSR: mindfulness-based stress reduction
PSS: Perceived Stress Scale
RCT: randomized controlled trial
REDCap: Research Electronic Data Capture
RiSE: Resilience, Stress, and Ethnicity
TNF-α: tumor necrosis factor–alpha
